## MATERIALS AND METHODS

### Study Design

RE-LuPSMA is an investigator-initiated, open-label, single-arm, single-center, phase 2 trial conducted at the UCLA. This trial is financially supported by Novartis, is being conducted under Investigational New Drug application 169476, and was approved by the UCLA institutional review board (IRB23-001509). The trial is registered at ClinicalTrials.gov (NCT06288113).

The study was powered to determine the 12-mo OS rate of patients with mCRPC who previously had a favorable response to a first regimen of [^177^Lu]Lu-PSMA-617 and are treated with rechallenge therapy (for a maximum of 6 additional cycles). We hypothesized a 12-mo OS rate of 71%, compared with a null hypothesis of an OS rate of 50% with no rechallenge therapy. The planned sample size is 40 subjects to achieve 80% power. The planned study duration is 45 mo. The study design is presented in Figure 1, and the patient flowchart is provided in Figure 2. The full study protocol is provided in the supplemental materials, available at http://jnm.snmjournals.org.

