### Endpoints

The primary endpoint is the 12-mo OS rate, measured from cycle 1 day 1 of [^177^Lu]Lu-PSMA-617 rechallenge therapy, which will be estimated using the Kaplan–Meier method with a 95% CI. A 1-sample log-rank test (as used in the power calculation) will be applied to assess whether the observed OS rate exceeds the null rate of 50%, derived from the standard care arm of the phase 3 VISION trial (1).

The secondary endpoints are as follows:
Overall and grade 3 or greater adverse-event rates, assessed using Common Terminology Criteria for Adverse Events version 5.0 through study completion.PSA response rate (response defined as a decline of ≥50% on 2 PSA levels measured at least 3 wk apart) during [^177^Lu]Lu-PSMA-617 rechallenge therapy.Biochemical PFS (defined by Prostate Cancer Working Group 3 guidelines as an increase of 25% and 2 ng/mL above the nadir, confirmed by a second value ≥ 3 wk later (11)) through rechallenge study completion.OS rate measured from the start of the first regimen of [^177^Lu]Lu-PSMA-617 RPT (cycle 1 day 1) through rechallenge study completion.OS rate measured from the end of the first regimen of [^177^Lu]Lu-PSMA-617 RPT (day 1 of the final cycle) through rechallenge study completion.Radiographic PFS through study completion, defined as progressive disease on prostate-specific membrane antigen (PSMA) PET/CT (Table 1) (12) or SPECT/CT Table 2 (13), assessed using response assessment criteria.Proportion of patients who initially had bone pain of at least 4/10 in severity who achieved a pain response (i.e., improvement of at least 2 points from baseline without an overall increase in opiate use) through rechallenge therapy completion.Median change in the Functional Assessment of Cancer Therapy–Radionuclide Therapy score (14) through study completion.Median change in the Brief Pain Inventory–Short Form score through rechallenge therapy completion.Median change in performance status, measured using the Eastern Cooperative Oncology Group performance score, through rechallenge therapy completion.

**TABLE 1. tbl1:** PSMA PET/CT Response Assessment Criteria

Response	Definition
Complete response	Absence of any PSMA uptake and no new PSMA-negative tumors
Partial response	>30% decrease in PSMA-VOL with no new PSMA-positive or -negative tumors

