### Eligibility Criteria

To qualify for enrollment, patients must meet all of the following inclusion criteria:
Age ≥ 18 y.Diagnosis of mCRPC.Prior regimen of chemotherapy for mCRPC allowed but not required.Previous treatment with at least 1 ARPI.Previous completion of 4–6 cycles of [^177^Lu]Lu-PSMA-617.Demonstration of favorable response to the first regimen of [^177^Lu]Lu-PSMA-617, defined as a decline of at least ≥ 50% in PSA level.Meets PSMA PET/CT VISION trial criteria (1): at least 1 lesion with PSMA uptake higher than that of the liver, no soft-tissue lesions larger than 1 cm with PSMA uptake less than or equal to the liver, PSMA PET/CT must be performed within 8 wk of the planned first cycle of rechallenge therapy and at least 6 wk after completion of the first regimen of [^177^Lu]Lu-PSMA-617.Eastern Cooperative Oncology Group performance score of 0–2.Sufficient bone marrow capacity (defined as white blood cells ≥ 2,500/μL, platelets ≥ 100,000/μL, hemoglobin ≥ 9.0 g/dL, and absolute neutrophil count ≥ 1,500/μL).Abilities to understand and sign an approved informed-consent form and comply with all protocol requirements.

Also, HIV-infected patients who have well-controlled HIV and a low risk of AIDS-related outcomes are eligible for inclusion.

Patients are not eligible for study inclusion if they have received myelosuppressive therapy or other RPT within the past 6 wk (including docetaxel, cabazitaxel, ^89^Sr, ^153^Sm, ^186^Re, ^188^Re, and ^223^Ra) or have an estimated glomerular filtration rate of less than 50 mL/min/1.73 m^2^.

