### Sample Size Determination and Stopping Rule

The primary endpoint of the study is the 12-mo OS rate starting from cycle 1 day 1 of rechallenge therapy. We hypothesize that patients retreated with [^177^Lu]Lu-PSMA-617 will have a 12-mo OS rate of 71% compared with a null hypothesis of 50% with no rechallenge therapy, based on the standard care group of the phase 3 VISION trial (1). A 2-sided, 1-sample log-rank test was used to estimate power. Assuming survival times follow an exponential distribution, a total of 40 subjects will achieve 80% power to detect a difference between a rechallenge group (71%) and a historic control group (50%), using a significance level of 0.05 (2-sided) and a follow-up duration of 24 mo after the last subject is enrolled. The complete statistical analysis plan is provided in section 11 of the study protocol.

The study incorporates a stopping rule mandating termination of the trial if treatment-related serious adverse events occur in 5 of the first 20 patients. If 4 or fewer such events occur among the first 20 patients, the trial can continue to completion. This rule was informed by an expected event rate of approximately 8% rate, as reported in prior retrospective series (6–10), using a 1-sample binomial test (1-sided α = 0.05).

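### The median change in ECOG score stays at zero until half the patients worsen, so the performance-status endpoint says little as defined

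*Protocol article*

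**What the plan says.** The last secondary endpoint listed in the protocol article (Endpoints) is "Median change in performance status, measured using the Eastern Cooperative Oncology Group performance score", assessed up to the end of rechallenge therapy. The summary statistic is therefore part of the endpoint definition and not a detail left to the analysis plan. Under Eligibility Criteria, patients must have an "Eastern Cooperative Oncology Group performance score of 0–2". On size, Study Design states: "The planned sample size is 40 subjects to achieve 80% power". That calculation concerns overall survival only. The article attaches no hypothesis, threshold or test to the ECOG endpoint.

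The same list handles bone pain differently: that endpoint is the proportion of patients who reach a defined pain response.

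**The concern.** A median suits a score with many possible values. ECOG has few, and over a course of treatment many patients can be expected to stay at their entry level, so many changes are ties at 0. The median then reports the tied value and ignores how many patients lie on either side of it. A third of the patients could lose a level of performance status and the endpoint would still read as no change.

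The trial has a single arm, so no control group would show that the summary barely moves. A reader of the results could take a median change of 0 as evidence that performance status was preserved, when it says only that fewer than half of the patients moved in one direction.

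**Working it through.** The article gives no figure for this endpoint, so there is none to reproduce. The check asks how the stated statistic behaves.

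**Inputs**
- n = 40 (Study Design), taking every enrolled patient as assessed.
- Whole-number score, entry values 0 to 2 (Eligibility Criteria).
- Assumption: a patient who worsens does so by one point. The true share worsening, q, is not given in the article, so a range is shown.

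**Step 1: where the median moves.** With n = 40 the median is the mean of the 20th and 21st ordered changes. Let k patients have a change of +1 and the rest 0.

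| k worse | 20th value | 21st value | Median |
|---|---|---|---|
| 19 (47.5%) | 0 | 0 | 0 |
| 20 (50%) | 0 | 1 | 0.5 |
| 21 (52.5%) | 1 | 1 | 1 |

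The results are the same when 4 or 8 of the other patients improve by one point. With fewer assessed the pattern holds: the median is still 0 with 14 of 30 or 9 of 20 worse.

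**Step 2: how often the median would show worsening.** The median exceeds 0 when at least 20 patients worsen. With X ~ Binomial(40, q), P(median > 0) = P(X ≥ 20) = 1 − P(X ≤ 19).

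| True share worsening, q | Expected number worse | P(median = 0) | P(median > 0) |
|---|---|---|---|
| 20% | 8 | above 99.9% | below 0.1% |
| 30% | 12 | 99.4% | 0.6% |
| 40% | 16 | 87.0% | 13.0% |
| 45% | 18 | 68.4% | 31.6% |

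Exactly 20 worse already lifts the median to 0.5, so that case belongs with P(median > 0).

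**Step 3: improvement.** By symmetry, the median falls below 0 only when at least 20 of 40 improve. Patients who enter at 0 cannot improve, so all 20 would have to come from those entering at 1 or 2.

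**Step 4: what a proportion would show.** Exact (Clopper-Pearson) 95% limits are the 2.5% quantile of Beta(k, n − k + 1) and the 97.5% quantile of Beta(k + 1, n − k).

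| Worse | Proportion | Exact 95% CI | Median change |
|---|---|---|---|
| 12 of 40 | 30.0% | 16.6% to 46.5% | 0 |
| 15 of 40 | 37.5% | 22.7% to 54.2% | 0 |
| 19 of 40 | 47.5% | 31.5% to 63.9% | 0 |

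Three clearly different outcomes share one value of the planned statistic.

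**The case against.** The strongest reply is that little depends on this endpoint. It is secondary and comes last in the list. Deterioration would also show elsewhere: death is the primary endpoint, and adverse-event rates, radiographic progression-free survival and the pain-response proportion are reported separately. The Discussion does rest part of the safety case on quality-of-life measures, but the Abstract names those as FACT-RNT and BPI-SF, not ECOG. Nothing in the article prevents the investigators from adding a table. All of this stands and limits the weight of the point. It does not make the ECOG median informative, and none of the other endpoints summarises change in performance status.

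A reader might go further and infer that the FACT-RNT endpoint, "Median change in the Functional Assessment of Cancer Therapy–Radionuclide Therapy score (14) through study completion", describes only survivors and so also hides decline. Attrition will be substantial late on. Under the article's exponential assumption, at about 31.5 months (24 months after a full course assumed to last 7.5 months), survival is 0.71^(31.5/12) = 41%, or 0.5^(31.5/12) = 16%. That is about 16 or 6 to 7 of 40. But the article does not say that this late visit is the one analysed, that only observed scores count, or how deaths are handled. The schedule figure and section 11 of the full protocol, where such rules would normally be found, are not shown. Loss through death would affect a mean as much as a median, and sticking at zero comes from a coarse scale, so it does not carry over to a questionnaire score. Nor is any fault shown for BPI-SF.

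**Conclusion.** The point holds for ECOG alone. As defined, the endpoint would report no change with up to 19 of 40 patients worse, and would do so about 99% of the time if 30% truly worsen and 87% of the time if 40% do. The threshold in patient numbers rests only on the whole-number scale, 40 assessed patients, and enough of the remaining patients staying at their entry level. The probabilities also assume that patients worsen independently with a common probability; the shares of 20% to 45% are illustrative and not taken from the article.

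The median is uninformative here; calling it wrong would be too strong for a descriptive secondary endpoint. Severity is minor. The primary endpoint, its test and the sample size are not affected.

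**What to change.** Redefine the ECOG endpoint, or add to it, as the proportion of patients whose score worsens by at least one point from baseline through completion of rechallenge therapy, with an exact 95% CI. Add a shift table of baseline against worst on-treatment score that gives the number assessed and lists deaths separately. The median can stay as a descriptive line. The FACT-RNT and BPI-SF wording need not change on this account.

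The cost is a change of endpoint wording and one extra table, using ECOG scores that the existing endpoint already requires. The reported picture may look less favourable than a median of 0.

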Stable disease	<30% decrease in PSMA-VOL (with or without new PSMA-positive or -negative tumors), ≥30% decrease in PSMA-VOL with new PSMA-positive or -negative tumors, <20% increase in PSMA-VOL (with or without new PSMA-positive or -negative tumors), or ≥20% increase in PSMA-VOL without new PSMA-positive or -negative tumors
Progressive disease	>30% increase in PSMA-VOL (with or without sites of PSMA-positive or -negative tumors)

PSMA-VOL = total volume of all PSMA-positive tumors.

Adapted from (12).

**TABLE 2. tbl2:** SPECT/CT Response Assessment Criteria

Response	Definition
Complete response	Absence of any PSMA uptake and no new PSMA-negative tumors
Partial response	>30% decrease in PSMA-VOL with no new PSMA-positive or -negative tumors
Stable disease	≤30% change in PSMA-VOL and no new PSMA-positive or -negative tumors
Progressive disease	>30% increase in PSMA-VOL (with or without new PSMA-positive tumors) or PSMA-negative tumors.

PSMA-VOL = total volume of all PSMA-positive tumors.

Adapted from (13).

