### Study Duration

Patients will be treated with up to 6 cycles of [^177^Lu]Lu-PSMA-617 rechallenge therapy. Treatment will be discontinued if there is evidence of biochemical (PSA increase of >25% and 2 ng/mL above nadir) and radiographic (progressive disease on PSMA PET/CT or SPECT/CT) progression, withdrawal of consent, noncompliance, unacceptable toxicity, or evidence that the patient is no longer benefiting or at the discretion of the investigator or sponsor.

The duration of subject participation will be from the time informed consent is provided through the 24 mo following completion of the final cycle of rechallenge therapy. The planned study duration is 45 mo. Study enrollment began August 2024, with an anticipated trial completion date of May 2028. The full schedule of visits and assessments is provided in Figure 3.

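### Table 1 (PSMA PET/CT) classes the same scan as both stable and progressive, so the radiographic PFS event is not uniquely defined

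*Protocol article*

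**What the plan says.** The Endpoints section of the protocol article lists as a secondary endpoint "Radiographic PFS through study completion, defined as progressive disease on prostate-specific membrane antigen (PSMA) PET/CT", and names SPECT as the alternative, with Table 1 for the former and Table 2 for the latter. The event is therefore whatever the progressive row of either table says it is.

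The Table 1 rows that matter are:

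- Partial response: ">30% decrease in PSMA-VOL with no new PSMA-positive or -negative tumors".
- Stable disease has four limbs. The first is "<30% decrease in PSMA-VOL (with or without new PSMA-positive or -negative tumors". The second is a decrease of 30% or more with new tumors. The third is an increase below 20%, regardless of new tumors. The fourth is "or ≥20% increase in PSMA-VOL without new PSMA-positive or -negative tumors".
- The row for progression reads ">30% increase in PSMA-VOL (with or without sites of PSMA-positive or -negative tumors".

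In Table 2, partial response is worded as in Table 1. Stable disease is "≤30% change in PSMA-VOL and no new PSMA-positive or -negative tumors". Progressive disease is an increase above 30%, or PSMA-negative tumors.

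The same categories appear under Study Duration. There, treatment ends on biochemical progression together with "radiographic (progressive disease on PSMA PET/CT or SPECT/CT) progression".

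**The concern.** A response table used to define a time-to-event endpoint must put every scan in one category and only one. Table 1 does not. Its stable row and its progressive row appear to express two different progression rules, and nothing says which prevails.

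The affected scans are not exotic. Growth of existing disease without a new lesion, and a new lesion with moderate growth, are ordinary ways for a scan to worsen. In an open-label single-arm trial, a definition that lets the reader settle the category after seeing the scan is an avoidable source of bias in a secondary endpoint. The same categories also feed one part of the rule for ending treatment.

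**Working it through.** No figure in the article needs reproducing; this is a logical check of the printed rows. Each row was turned into a condition on the percentage change in PSMA-VOL and on the presence of new tumors. Changes from −100% to +100% were then classified in 1-point steps.

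**Table 1 (PET)**

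| Change in PSMA-VOL | No new tumor | Any new tumor |
|---|---|---|
| Decrease above 30%, some uptake left | Partial response | Stable |
| Decrease of exactly 30% | **No row** | Stable |
| Decrease under 30% to increase under 20% | Stable | Stable |
| Increase of 20% to 30% | Stable | **No row** |
| Increase above 30% | **Stable and progressive** | Progressive |

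An example for the last row is an increase of 50% with no new tumor. Since 50 ≥ 20 and nothing is new, the fourth stable limb is met. Since 50 > 30, the progressive row is met too.

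An example for the row above it is an increase of 25% with a new tumor. Since 25 is not below 20, the third stable limb fails. The fourth fails because a tumor is new. Since 25 is not above 30, the progressive row fails.

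**The two rules behind Table 1**

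- Rule A is what the stable row leaves over on the increase side: an increase of at least 20% with new tumors.
- Rule B is the progressive row as printed: an increase above 30%, new tumors or not.

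| Scan | Rule A | Rule B |
|---|---|---|
| Above 30%, new tumor | Event | Event |
| Above 30%, no new tumor | Non-event | Event |
| 20–30%, new tumor | Event | Non-event |

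The rules differ in two cells, in opposite directions. Choosing one over the other could therefore lengthen or shorten radiographic PFS, and the article gives no basis for signing the net effect.

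**Table 2 (SPECT)**, reading its PSMA-negative clause as new PSMA-negative tumors:

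| Change in PSMA-VOL | No new tumor | New PSMA-positive only | New PSMA-negative |
|---|---|---|---|
| Decrease above 30%, some uptake left | Partial response | **No row** | Progressive |
| Change within 30% either way | Stable | **No row** | Progressive |
| Increase above 30% | Progressive | Progressive | Progressive |

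On this reading Table 2 has a gap but no overlap between stable and progressive.

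**Exposure.** The Investigational Plan schedules PET in cycles 2, 4 and 6, so Table 1 is applied to at most 3 × 40 = 120 on-treatment PET scans. This is a ceiling on the scans to be read, not an estimate of those misclassified.

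**The case against.** The strongest reply is that the event is progressive disease, so only the progressive row needs to be read. Under that reading, growth above 30% is always an event, and a scan that fits no row is simply a non-event. This stands for the minor gaps: a decrease of exactly 30% in Table 1, and the new PSMA-positive lesion in Table 2, affect response categories rather than the PFS event as printed. It does not settle Table 1, because the article states no precedence and the stable row expressly calls the same scan stable.

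A second reply is that SPECT, done every cycle, applies an unambiguous threshold of more than 30% and so partly backs up the PET reading. That is fair, but it does not remove the contradiction in a table that can supply the event by itself.

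A reader might infer more than the article supports:

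- *That radiographic PFS cannot be derived at all.* The conflict concerns particular PET scans, not all of them.
- *That SPECT also has a stable/progressive overlap.* This arises only if the PSMA-negative clause of Table 2 is taken to include pre-existing tumors, because the word for new is not repeated there. The gap is firm; the overlap is not.
- *That deaths are not PFS events.* The Endpoints list names none, but it is condensed and shows no censoring rule. The full protocol and its analysis section, not shown, may define this, so no finding is made.
- *That an ambiguous scan by itself ends treatment.* Study Duration requires biochemical and radiographic progression together for that criterion.

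**Conclusion.** The point holds for Table 1. An increase above 30% without new tumors is both stable and progressive. An increase of 20–30% with new tumors has no category, although the stable row implies it is progression. This is a contradiction between two rows printed in full, not detail left to another document, and the rows read as complete statements, so damage in text extraction is unlikely.

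The effect is confined to a secondary endpoint, to response categories, and to the radiographic half of one discontinuation criterion. The 12-month overall survival endpoint and the sample size of 40 use neither table. The number of scans affected, and the direction of any shift in radiographic PFS, cannot be determined from the article.

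**What to change.** Before scans are analysed:

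1. Reconcile the stable and progressive rows of Table 1 against the criteria from which the table was adapted, so that one progression rule remains and every scan falls in exactly one category. Include the decrease of exactly 30%.
2. In Table 2, assign to a row the scans with a new PSMA-positive tumor, no PSMA-negative tumor and no increase above 30%. State whether the PSMA-negative clause means new tumors only.
3. Reconcile the discontinuation criterion under Study Duration with the corrected tables, since it uses the same categories. Which threshold is right is for the sponsor and the cited criteria to settle and is not judged here.

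The cost is an edit to two tables and a cross-check of one paragraph. Any scan already classified in an affected cell would need to be reclassified under the corrected rows. Sample size and the primary analysis do not change.

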### Eligibility Criteria

To qualify for enrollment, patients must meet all of the following inclusion criteria:
Age ≥ 18 y.Diagnosis of mCRPC.Prior regimen of chemotherapy for mCRPC allowed but not required.Previous treatment with at least 1 ARPI.Previous completion of 4–6 cycles of [^177^Lu]Lu-PSMA-617.Demonstration of favorable response to the first regimen of [^177^Lu]Lu-PSMA-617, defined as a decline of at least ≥ 50% in PSA level.Meets PSMA PET/CT VISION trial criteria (1): at least 1 lesion with PSMA uptake higher than that of the liver, no soft-tissue lesions larger than 1 cm with PSMA uptake less than or equal to the liver, PSMA PET/CT must be performed within 8 wk of the planned first cycle of rechallenge therapy and at least 6 wk after completion of the first regimen of [^177^Lu]Lu-PSMA-617.Eastern Cooperative Oncology Group performance score of 0–2.Sufficient bone marrow capacity (defined as white blood cells ≥ 2,500/μL, platelets ≥ 100,000/μL, hemoglobin ≥ 9.0 g/dL, and absolute neutrophil count ≥ 1,500/μL).Abilities to understand and sign an approved informed-consent form and comply with all protocol requirements.

Also, HIV-infected patients who have well-controlled HIV and a low risk of AIDS-related outcomes are eligible for inclusion.

Patients are not eligible for study inclusion if they have received myelosuppressive therapy or other RPT within the past 6 wk (including docetaxel, cabazitaxel, ^89^Sr, ^153^Sm, ^186^Re, ^188^Re, and ^223^Ra) or have an estimated glomerular filtration rate of less than 50 mL/min/1.73 m^2^.

